### MRI interpretation in ART-Pro-2

3.7

ART-Pro-2 will be conducted retrospectively and will not impact patient care. Radiologists will be categorized by level of experience for prostate MRI based on the joint European Society of Urogenital Radiologists (ESUR) and the EAU Section of Urological Imaging (ESUI) criteria: novice prostate radiologists defined as having read <400 cases, basic prostate radiologists defined as having read ≥400 and <1000 cases, and expert prostate radiologists defined as having read ≥1000 cases [11]. The design of ART-Pro-2 in evaluating nonexpert readers retrospectively allows for “locking” of reader experience level, whereas if evaluated over the ART-Pro-1 trial period, readers could change (by criteria) from being novice to basic and/or expert. Each radiologist will be provided a list of 100 patient cases to review, 50 with mpMRI and 50 with RSIrs plus mpMRI. Case lists will be generated as random permutations of cases while requiring that (1) no radiologist be assigned cases from the institution where he/she works (to ensure that the radiologist has not seen the cases before), (2) each patient case is assigned to at least three radiologists as mpMRI (one from each of the experience levels), and (3) each patient case is assigned to at least three (different) radiologists (one from each of the experience levels) as RSIrs plus mpMRI. Thus, each patient case will be reviewed by six radiologists (two from each of the experience levels). Image sets will be provided as sessions using the MIM Zero Footprint platform (MIM Software, Cleveland, OH, USA) to facilitate individual work lists and presentation of image subsets.

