### Analyses for ART-Pro-2

4.2

Statistical analyses for ART-Pro-2 will be analogous to those described for ART-Pro-1. In ART-Pro-2, each radiologist will give sequential reports on each assigned patient case, that is, either (1) bpMRI and (2) mpMRI or (3) RSIrs plus T2W axial, (4) RSIrs plus bpMRI, and (5) RSIrs plus mpMRI. We will compare each approach (1 and 3–5) to mpMRI in an analogous manner to that in ART-Pro-1 using McNemar’s test and AUCs. These analyses will be performed within each stratum of ESUR radiologist expertise, testing for noninferiority compared with mpMRI PI-RADS for ESUR-defined experts (essentially a validation of ART-Pro-1), radiologists with basic prostate MRI proficiency, and novices. In terms of statistical power, each of these ART-Pro-2 subgroups will have the same statistical power as the primary and key secondary analyses of ART-Pro-1.

Additionally, we will estimate the effect of radiologist expertise for each approach (1–5) in linear mixed-effect models that utilize all the data from ART-Pro-2. Models will take the following form:csPCastatusscore+experience+(1|patient)+(1|radiologist)

Here, csPCa status is whether the patient was diagnosed with csPCa (binary), score is the PI-RADS or Likert score assigned, and experience is a categorical variable for ESUR/ESUI level of experience. Importance of radiologist experience within each approach (1–5) will be estimated by the parameter estimates for ESUR/ESUI basic proficiency and ESUR/ESUI novice levels, compared with a reference of ESUR/ESUI experts.

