### Secondary analyses

4.3

We will repeat statistical analyses above using an alternate definition of grade group (GG) ≥3 as true positives. GG 1 or benign will continue to be considered true negatives. We will also measure the detection of cancers of each GG (GG 1, 2, 3, or 4–5). GG 1 diagnoses will be considered undesirable overdiagnoses. Rates of overdiagnosis will be compared by McNemar’s test, as above.

The percentage of cases with diagnostic quality imaging as per PI-QUAL (as rated by reader 1 in ART-Pro-1) will be measured for each site and for the study, overall. The percentage of cases with significant distortion of DWI will be measured for each site and for the study, overall. The percentage of such cases where distortion correction was deemed diagnostically helpful will be measured for each site and for the study, overall.

Inter-reader reliability of PI-QUAL and bpMRI PI-RADS scores will be summarized using Cohen’s kappa, comparing ART-Pro-1 reader 1 with ART-Pro-1 reader 2.

We will calculate the percentage of csPCa detected on systemic biopsy only, targeted biopsy only, or both.

Radiologists estimate the probability of csPCa on biopsy for each patient and record this in the REDCap forms. We have previously reported objective estimates of probability of csPCa for RSIrs maximum in the prostate [35]. For ART-Pro patients who undergo biopsy, we will construct ROC curves for radiologists’ and RSIrs estimates, with 95% CIs via bootstrapping. We will compare discriminative performance for expert radiologists, nonexpert radiologists, and RSIrs. We will also visualize calibration for each of these via qq plots [43].

In ART-Pro-2, the overall performance of each approach (1–5) will also be compared by measuring the Akaike information criterion for each model.

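### The additional ART-Pro-2 expertise model puts a fixed patient diagnosis on the left with a patient random intercept, so it has no maximum likelihood solution, and its experience coefficient does not measure accuracy

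*Protocol article*

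**What the plan says.** Section 4.2 (Analyses for ART-Pro-2) first sets out noninferiority tests within each experience stratum. It then adds a second analysis: "we will estimate the effect of radiologist expertise for each approach (1–5) in linear mixed-effect models that utilize all the data from ART-Pro-2". The formula is printed as "csPCastatusscore+experience+(1|patient)+(1|radiologist" and a closing bracket. The sign between response and predictors does not show in the text version, but the order of terms and the definitions ("csPCa status is whether the patient was diagnosed with csPCa (binary), score is the PI-RADS or Likert score assigned") make csPCa status the response. Experience enters as a main effect only, with no score-by-experience interaction. Its importance within each approach "will be estimated by the parameter estimates for ESUR/ESUI basic proficiency and ESUR/ESUI novice levels, compared with a reference of ESUR/ESUI experts".

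Section 3.7 (MRI interpretation in ART-Pro-2) fixes the reading design: "each patient case is assigned to at least three radiologists as mpMRI (one from each of the experience levels"), and likewise, with different radiologists, for RSIrs plus mpMRI. Each case therefore has six reads, two per experience level.

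Section 4.3 (Secondary analyses) uses the same models again: the overall performance of approaches 1 to 5 is to be "compared by measuring the Akaike information criterion for each model".

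**The concern.** csPCa status belongs to the patient. It cannot vary between the three reads of that patient within an approach. A random intercept per patient can therefore fit the response perfectly and leaves nothing for score or experience to explain.

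There is a second difficulty. Every level reads every patient, so csPCa prevalence is the same at each level by design. A main effect of experience on csPCa status then has no difference in outcome to describe, and the question is what the coefficient measures instead.

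At stake are the model meant to estimate the expertise effect for each approach from all ART-Pro-2 data, and the single-index comparison of the five approaches. Dependence on reader expertise is one of the two barriers that the trial sets out to address.

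**Working it through.** The plan states no figure for this model, so there is none to reproduce. The check concerns its structure.

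**Inputs from the article.** 500 patients (section 2.3); expected csPCa prevalence 30% (section 4.1.2); three reads per patient within each approach, one per level (section 3.7). That gives 500 × 3 = 1,500 rows per model. **Assumed for the simulations only:** 10 readers per level (500 × 6 reads / 100 cases = 30 readers) and five-level scores cut from a latent normal variable.

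**Step 1. Likelihood of the linear model.** Take n = 500, m = 3, patient variance σp², residual variance σe², and reader variance at 0, which is a permitted boundary value. Then

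log L = -½ [ nm ln(2π) + n ln(σe² + mσp²) + n(m-1) ln(σe²) + m Σ r̄² / (σe² + mσp²) + W/σe² ],

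where r̄ is a patient's mean residual and W the within-patient sum of squares. Set the score and experience slopes to 0. The response is constant within patient, so W = 0 exactly. The term -½ n(m-1) ln(σe²) = -1,000 ln(σe) then grows without limit as σe goes to 0, by 1,000 × ln 10 = 2,303 per tenfold fall.

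In one simulated dataset (AIC with 4 fixed effects and 3 variances):

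| σe | log L | AIC |
|---|---|---|
| 0.1 | 782 | -1,549 |
| 0.01 | 3,084 | -6,154 |
| 0.001 | 5,387 | -10,760 |
| 10⁻⁸ | 16,900 | -33,786 |

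Profiling over the ratio σp²/σe² with the slopes free gives the same picture:

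| Ratio | Score slope | Basic coefficient | log L |
|---|---|---|---|
| 0 | 0.186 | 0.0205 | -738 |
| 1 | 0.104 | 0.0114 | -162 |
| 10 | 0.021 | 0.0023 | 759 |
| 10⁶ | 0.000 | 0.000 | 6,475 |

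There is no maximum. AIC has no defined value, and any number reported depends on where the optimiser stops.

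**Step 2. Logistic variant.** Holding the patient SD at fixed values, the log-likelihood was -706 at 0.01, -337 at 10, -317 at 30 and -312 at 100, still rising at the largest value tried. The score coefficient went from 1.1 to 10.8. A logistic likelihood cannot exceed 0, so it is bounded, but no usable finite estimate was reached.

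**Step 3. What the experience coefficient measures.** In a least-squares fit with level dummies, mean(y) at a level = intercept + b × mean(score) + c for that level. Subtracting the expert equation:

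c(novice) = [difference in mean y] - b × [difference in mean score].

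The first bracket is 0 because each level reads the same patients. Hence c = -b × (difference in mean score). The profile in Step 1 is consistent with this: the basic coefficient divided by the score slope is 0.110 at ratios 0, 1 and 10.

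Means over 200 simulated datasets per scenario, fitted by ordinary least squares without random intercepts:

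| Scenario | AUC expert / novice | Mean score expert / novice | b | Novice coefficient |
|---|---|---|---|---|
| Same underlying discrimination, novices overcall | 0.835 / 0.808 | 3.12 / 3.80 | 0.190 | -0.129 |
| Novices less accurate, mean scores nearly matched | 0.898 / 0.697 | 3.23 / 3.30 | 0.178 | -0.013 |
| Novices at chance, mean scores nearly matched | 0.898 / 0.497 | 3.23 / 3.31 | 0.131 | -0.011 |

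The first row checks by hand: -0.190 × (3.80 - 3.12) = -0.129. The largest coefficient goes with the smallest loss of accuracy.

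**The case against.** The strongest reply is about scope, and it stands. Section 4.2 introduces this model as an addition, and the AIC comparison sits under secondary analyses. Three readings go further than the article supports.

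- *A reader might infer that ART-Pro-2 has no other analysis of expertise.* Section 4.2 runs McNemar and AUC noninferiority tests separately for experts, basic readers and novices. Section 4.3 compares the discrimination of expert and nonexpert probability estimates by ROC curves with bootstrap intervals in biopsied patients. Novices near chance should show up there.
- *A reader might infer that AIC is the only comparison of the approaches.* Section 4.2 also tests approaches 1 and 3–5 against mpMRI; AIC is supplementary to that.
- *A reader might infer that the primary or key secondary conclusions are at risk.* Their planned McNemar and AUC tests do not use this model.

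It can also be said that a linear model for a binary outcome is a recognised choice. That is so, and it is not the fault here; the fault is a response that is constant within patient. The condensed article may use the word linear loosely, but the logistic version does not yield usable estimates either. Finally, the analyst would probably see a singular or non-converged fit, so a silent error is less likely. That leaves the planned analysis without a result, and dropping the patient term to obtain convergence leads to the coefficient in Step 3.

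**Conclusion.** The point holds for the additional expertise model and the AIC comparison, and for nothing else. As a linear mixed model it has an unbounded likelihood, with the score slope and experience coefficients going to 0. As a logistic mixed model the patient variance and coefficients drift upward without a usable finite estimate. With the patient term removed, the experience coefficient is minus the score slope times the difference in mean score, which reflects over- or under-scoring and not accuracy.

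The divergence of the linear model and the coefficient identity follow from the stated model and reading design. They do not depend on assumed reader behaviour. The AUCs and coefficients in Step 3, and the logistic figures, come from simulations with assumed reader parameters and illustrate the size only. The Step 3 coefficients come from a reduced model, not the printed one. They are close to 0 in two scenarios because mean scores there were nearly matched, so they do not show that the coefficient is always near 0.

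**What to change.** For each approach, make the reading the outcome: either binary positive MRI with a logistic link or the ordinal score with a cumulative-logit link. Use csPCa status, experience and their interaction as predictors, with crossed random intercepts for patient and radiologist. The interaction lets a difference in discrimination between levels appear. Report sensitivity and specificity at each level, and their differences from experts, with confidence intervals.

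Replace the AIC comparison with multireader-multicase AUC differences between approaches, with confidence intervals. The method must allow for a design that is not fully crossed, because each radiologist reads 100 cases, 50 in each arm.

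The cost is revised wording in sections 4.2 and 4.3 and slightly more analysis work. The same reads and patients are used, and no sample size or other test changes.

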### Secondary analyses

4.3

We will repeat statistical analyses above using an alternate definition of grade group (GG) ≥3 as true positives. GG 1 or benign will continue to be considered true negatives. We will also measure the detection of cancers of each GG (GG 1, 2, 3, or 4–5). GG 1 diagnoses will be considered undesirable overdiagnoses. Rates of overdiagnosis will be compared by McNemar’s test, as above.

The percentage of cases with diagnostic quality imaging as per PI-QUAL (as rated by reader 1 in ART-Pro-1) will be measured for each site and for the study, overall. The percentage of cases with significant distortion of DWI will be measured for each site and for the study, overall. The percentage of such cases where distortion correction was deemed diagnostically helpful will be measured for each site and for the study, overall.

Inter-reader reliability of PI-QUAL and bpMRI PI-RADS scores will be summarized using Cohen’s kappa, comparing ART-Pro-1 reader 1 with ART-Pro-1 reader 2.

We will calculate the percentage of csPCa detected on systemic biopsy only, targeted biopsy only, or both.

Radiologists estimate the probability of csPCa on biopsy for each patient and record this in the REDCap forms. We have previously reported objective estimates of probability of csPCa for RSIrs maximum in the prostate [35]. For ART-Pro patients who undergo biopsy, we will construct ROC curves for radiologists’ and RSIrs estimates, with 95% CIs via bootstrapping. We will compare discriminative performance for expert radiologists, nonexpert radiologists, and RSIrs. We will also visualize calibration for each of these via qq plots [43].

In ART-Pro-2, the overall performance of each approach (1–5) will also be compared by measuring the Akaike information criterion for each model.

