### Objectives

2.2

The primary and secondary objectives are listed in Table 1.

**Table 1 t0005:** Study objectives

*Primary objectives*
1. Evaluate if bpMRI is noninferior to mpMRI among expert (ART-Pro-1) and nonexpert (ART-Pro-2) radiologists for the detection of GG ≥2 csPCa
*Secondary objectives*
1. Evaluate if RSIrs plus axial *T_2_*-weighted MRI is noninferior to mpMRI among expert and nonexpert radiologists for the detection of GG ≥2 csPCa a
2. Compare quantitative RSIrs (objective interpretation) with qualitative mpMRI (subjective radiologist interpretation) for the detection of GG ≥2 csPCa a
3. Evaluate bpMRI, mpMRI, and RSIrs for avoidance of unnecessary biopsies (ie, any biopsy resulting in no cancer or only GG 1) a
4. Evaluate bpMRI, mpMRI, and RSIrs for the detection of GG ≥3 cancer
5. Assess performance of the above MRI techniques for the detection of each: GG 1 (overdiagnosis), GG 2, GG 3, and GG 4–5
6. Evaluate the quality of scan images: a. Percentage of cases with diagnostic quality imaging as per PI-QUAL b. Percentage of cases with moderate or severe distortion i. Percentage of cases where distortion correction is useful
7. Evaluate csPCa detection by targeted vs systematic biopsy cores
8. Measure inter-reader reliability of bpMRI and mpMRI
9. Evaluate accuracy of radiologists’ and RSIrs-based estimates of overall probability of csPCa on biopsy
10. Assess influence of RSIrs on bpMRI interpretation

bpMRI = biparametric MRI; csPCa = clinically significant prostate cancer; GG = grade group; mpMRI = multiparametric MRI; MRI = magnetic resonance imaging; PI-QUAL = Prostate Imaging Quality; RSIrs = Restriction Spectrum Imaging restriction score.

a Key secondary objectives.

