### Image distribution and processing

3.4

Images from within each institution’s health IT network are transmitted from their scanner(s) to a processing/routing system created for ART-Pro. This system creates and processes two subsets of images, one for reader 1 and one for reader 2. The subset for reader 1 includes the standard of care mpMRI sequences (DWI, T2W, and DCE). These images are fully identifiable with the patient ID and are no different from standard of care images when sent to PACS. The subset for reader 2 includes bpMRI (without DCE) and RSIrs; these are deidentified and assigned an anonymized ID before being sent back to PACS. This deidentified work list for reader 2 ensures that reader 2 does not inadvertently view the full set of mpMRI images and/or interfere with reader 1’s clinical work list essential for clinical reporting. The processing system generates RSIrs maps using the internal MATLAB code developed by the investigator team and described previously [27], [28], [34], [35]. Briefly, the multidirection (tensor), multi-*b*-value diffusion-weighted images are corrected for image distortions arising from *B_0_*-field inhomogeneity, gradient nonlinearity, and eddy currents. Background noise and receiver coil bias are then removed. The corrected data are fit to a multicompartment RSI model, and the signal from the slowest diffusion compartment is normalized by the median signal within the prostate on the *b* = 0 s/mm^2^ images to generate RSIrs maps. RSIrs maps from both short TE scans are averaged together to generate the final RSIrs map that is distributed to the radiologists.

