### MRI interpretation in ART-Pro-1

3.5

MRI examinations are evaluated by two expert radiologists at the imaging center, with each radiologist interpreting approximately half of the cases in the role of reader 1 and half in the role of reader 2 (either by random assignment or by which radiologist happens to be on clinical service the day the patient is scanned). Reporting of MRI examinations is done as the per PI-RADS v2.1 guidelines. Both readers also assess the quality of each modality reviewed (T2W, DWI, and DCE). Both readers know the clinical indication for the prostate MRI examination given by the ordering physician. Both also have access to the patient’s electronic medical record for age, race, ethnicity, family history, prostate-specific antigen level, prior biopsy information, etc. Both readers record whatever clinical information they reviewed by copying it into their research reports in our centralized REDCap database.

#### Reader 1

3.5.1

Reader 1 fills out a research report (Reader 1 Report; see the Supplementary material), captured and stored in our centralized REDCap database, of the MRI findings. Reader 1 is first blinded to the DCE sequence and reports the MRI using only the biparametric (T2W and DWI) sequences. After reporting the bpMRI, reader 1 is unblinded to the DCE sequence and re-reports the MRI using the full mpMRI (T2W, DWI, and DCE) sequences. Reader 1 cannot go back and change his/her response for own bpMRI findings, so reader 1 ultimately provides two research reads: one without DCE and one with DCE. For both the bpMRI and mpMRI reports, reader 1 provides an overall estimate of the probability of csPCa per lesion and per patient.

#### Reader 2

3.5.2

While blinded to the findings of reader 1, reader 2 completes a separate research report using bpMRI and RSIrs (Reader 2 Report; see the Supplementary material), captured and stored in our centralized REDCap database. Lesions are assessed according to PI-RADS v2.1 with bpMRI; additionally, reader 2 reports the maximum RSIrs for each lesion. Reader 2 also provides an overall estimate of the probability of csPCa per lesion and per patient.

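### The planned inter-reader kappa cannot give the mpMRI reliability that objective 8 promises, and its bpMRI estimate mixes reader variation with any RSIrs effect

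*Protocol article*

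**What the plan says.** All references are to the protocol article.

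- **Section 2.2, Table 1, objective 8:** "Measure inter-reader reliability of bpMRI and mpMRI". It does not carry the footnote that marks key secondary objectives.
- **Section 4.3:** "Inter-reader reliability of PI-QUAL and bpMRI PI-RADS scores will be summarized using" Cohen's kappa, "comparing ART-Pro-1 reader 1 with ART-Pro-1 reader 2". No other agreement analysis is described for either stage. Section 4.2 describes McNemar's tests, AUCs and mixed models for ART-Pro-2.
- **Section 3.5.1, reader 1:** this reader first "reports the MRI using only the biparametric (T2W and DWI) sequences", then re-reports with DCE. The first read is locked: "Reader 1 cannot go back and change his/her response for own bpMRI findings".
- **Section 3.5.2, reader 2:** "reader 2 completes a separate research report using bpMRI and RSIrs". On scoring: "Lesions are assessed according to PI-RADS v2.1 with bpMRI; additionally, reader 2 reports the maximum RSIrs for each lesion".
- **Section 3.4, images supplied:** "The subset for reader 2 includes bpMRI (without DCE) and RSIrs". The separate work list is meant to keep reader 2 from seeing the full mpMRI set.

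**The concern.** An inter-reader reliability estimate for a technique needs two readers who each read the same case with that technique. The pair named in section 4.3 does not meet this for mpMRI, and meets it only nominally for bpMRI.

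Dependence on reader expertise is one of the two barriers the trial sets out to address. If section 4.3 is followed as written, the report will contain no mpMRI reliability. It will also contain a figure labelled bpMRI reliability in which a change of reader and a change of available images occur together. The two techniques then could not be compared on reliability, although objective 8 names both.

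**Working it through.** The documents state no kappa, precision target or sample size for reliability, so there is no figure to reproduce. The check is a count of usable reads per case, followed by a comparison of what each reader had in view.

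**Step 1: mpMRI pairs in ART-Pro-1.** Inputs are sections 3.4, 3.5.1 and 3.5.2. Independent mpMRI research reads per case: reader 1 = 1, reader 2 = 0. With n reads the number of reader pairs is n(n − 1)/2, so 1 × 0/2 = 0. The named comparison cannot give an mpMRI kappa.

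The re-evaluation in section 3.5.3 does not help. It is reader 1's own update after seeing reader 2's report, so it is neither a second reader nor an independent read.

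**Step 2: RSIrs-free bpMRI pairs in ART-Pro-1.** Reader 1 contributes one such read, locked before DCE is shown. Reader 2 contributes one report made from bpMRI and RSIrs supplied together, and no earlier locked bpMRI score is described. On the article's text the number of pairs in which both reads are demonstrably RSIrs-free is again 1 × 0/2 = 0.

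**Step 3: what the planned bpMRI kappa compares.**

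| | Reader 1, first report | Reader 2, report |
|---|---|---|
| T2W and DWI | yes | yes |
| RSIrs maps in view | no | yes |
| Score locked before further images | yes | not described |

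Reader and image set change together in every case. Section 3.5 has each radiologist take each role in about half the cases. That balances individuals across roles, but RSIrs always goes with the reader 2 role, so the exchange does not separate the two sources of disagreement. RSIrs could break agreement that would otherwise exist, or restore agreement that would otherwise be missing. The sign of any bias is therefore unknown, as is its size. Objective 10, on whether RSIrs influences how bpMRI is read, shows that the trial treats such an effect as possible.

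**Step 4: RSIrs-free reads elsewhere in the plan.** Section 3.7 assigns each case to at least three radiologists in the ART-Pro-2 mpMRI pathway, one per experience level. Section 3.7.1 has each of them report bpMRI and then mpMRI, without RSIrs.

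- Within ART-Pro-2: at least 3 × 2/2 = 3 pairs per case for each technique (expert–basic, expert–novice, basic–novice).
- Across stages: ART-Pro-1 reader 1 with the ART-Pro-2 expert gives at least one expert–expert pair per case for each technique. Section 3.7 bars radiologists from cases of their own institution, so the two are different people.

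The data needed for objective 8 are thus already planned, but section 4.3 does not use them for reliability.

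**The case against.** The strongest reply is that section 3.5.2 defines reader 2's PI-RADS score on bpMRI and treats the maximum RSIrs as an added field, and that section 4.1.1 calls the reading reader 2 bpMRI. The Reader 2 form is in the supplement and is not shown; it may require a bpMRI score before RSIrs is displayed. This has weight. It rules out saying flatly that the kappa does not measure bpMRI reliability, and it makes the second half of the point conditional. It does not remove that half, because naming the scoring system does not blind the reader, and the article states a lock for reader 1 but none for reader 2. It leaves the mpMRI half untouched.

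A second reply is that reader dependence is studied mainly through the experience-stratified tests and mixed models of section 4.2. That is fair, and it limits the importance of the point. Those analyses address accuracy and the effect of experience, however, and not agreement between readers.

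Some stronger readings are tempting, but the documents do not support them:

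- *That the kappa is unweighted.* Section 4.3 says only Cohen's kappa. Weighting is a detail that an analysis plan can settle.
- *That the PI-QUAL comparison is invalid because reader 2 sees no DCE.* Section 3.5 has both readers rate each modality they review, so ratings of the shared sequences exist. Nothing says that overall ratings resting on different sequences will be compared.
- *That the trial expects RSIrs to change experts' calls.* Objective 10 only asks about influence, the hypothesis in section 4 about adding RSIrs concerns nonexperts, and section 4.1.2 assumes a true difference of 0% for the paired expert comparisons. Zero net difference does not exclude changed calls in individual patients, but it is not an expectation of change.
- *That the kappa is biased downward by a stated amount.* No document figure supports a size or a direction.

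**Conclusion.** The point holds in two parts of different certainty.

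1. **mpMRI: certain from the text.** Objective 8 promises mpMRI reliability, section 4.3 names no mpMRI score, and the named pair gives zero mpMRI reader pairs. This is a mismatch between a stated objective and a stated analysis, not a detail left to a fuller document: the article fixes the scores, the statistic and the reader pair. A reader might infer that the trial as a whole cannot deliver mpMRI reliability. That goes too far, since the ART-Pro-2 reads can supply it.
2. **bpMRI: holds on the article's description.** The kappa mixes reader variation with any RSIrs effect, of unknown size and direction. This rests on reader 2 having RSIrs in view while scoring, with no locked RSIrs-free step. It would weaken if the Reader 2 form provides one.

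The consequence is confined to a non-key secondary objective. No primary or key secondary result and no sample size is affected. The change is still worth making, because otherwise half of the objective goes unanswered and the other half is reported under a label that the described design does not support.

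**What to change.** In section 4.3, or in the analysis plan with a matching statement:

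1. Estimate bpMRI and mpMRI reliability separately, with confidence intervals, from RSIrs-free reads already planned: (a) agreement among the ART-Pro-2 mpMRI-pathway readers of the same case, across experience levels; and (b) ART-Pro-1 reader 1 versus the ART-Pro-2 expert in that pathway.
2. Keep the reader 1 versus reader 2 kappa, but label it agreement of bpMRI with bpMRI plus RSIrs. If the Reader 2 form does lock a bpMRI score before RSIrs is shown, say so in section 3.5.2; the present label can then stand.
3. If no mpMRI agreement analysis is wanted, narrow objective 8 to bpMRI.

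The cost is some wording and a small additional analysis, with no new reads. There are two limitations to state. Comparison (a) has no guaranteed pair at the same experience level, so it describes agreement between levels. Comparison (b) also reflects setting: reader 1 reads prospectively at the home site with access to the medical record, while the ART-Pro-2 expert reads retrospectively, from another institution, with no record access described.
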